### Provisions for post-trial care {30}

There is no anticipated harm and compensation for trial participation. Patients will undergo routine follow-ups with their cardiologist, and participation in the study will stop at 6 months after CTO-PCI.

### Outcomes {12}

The primary objective of this study is to compare rates of successful wire crossing in ≤60 min in complex CTO (J-CTO ≥2) among the CT group and angiography group. Wire crossing will be considered successful if TIMI flow 3 is restored and residual stenosis is <30%. TIMI flow and residual stenosis will be evaluated by a pool of two cardiologists who are not directly involved in the procedure, and who are blinded to group allocation. The TIMI flow scale is classified as Grade 0 to 3 (Table 1).

**Table 1 Tab1:** TIMI flow grades

Grade 0	No flow
Grade 1	penetration without perfusion in the distal part of the artery
Grade 2	partial perfusion, the iodine contrast goes across the obstruction and fills the distal part of the artery, but the flow and the clearance of the iodine contrast are perceptibly slower if compared to the other non-occluded segments/arteries
Grade 3	complete perfusion, anterograde flow into the distal part of the artery with rapid filling and clearance if compared to the other segments/arteries.

The secondary objectives of the study are to compare:Success rates at any timeTotal time of PCI (minutes)Time of wire crossingRate of PCI complications (Major Adverse Cardiac Events, MACE): death, coronary perforation with cardiac tamponade requiring pericardiocentesis, myocardial infarction (if elevation of troponin or creatine kinase associated with change in electrocardiogram), stroke, major bleeding with loss of haemoglobin > 3 g/dl.Radiation levels during PCI expressed as transferred kinetic energy (air Kerma, Gy), dose area product (DAP, mGycm^2^), and fluoroscopy time (minutes).Volume of iodine contrast medium administered during PCI (millilitres).Cost of the PCI (euros) CTTA (CT group) Angiography Preoperative assessment, as summarised in the material invoice of every procedure.

Renal adverse events will be assessed after diagnostic coronary angiography, CCTA (CT group only), and CTO-PCI. Clinically relevant findings (like contrast allergic reaction) will be reported as adverse events. Their relationship with the CT scan or CTO-PCI will be reported. Other symptoms, such as angina CCS class, dyspnea NYHA class, MACE and renal failure will be recorded. Biologic markers, such as troponin, creatine kinase, creatinine, clearance of creatinine, and haemoglobin, will be recorded after CTO-PCI.

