**Methods:**

This is a randomised controlled open-label multi-centre trial in a superiority framework with 1:1 allocation ratio. Participants (*n* = 130) will be randomised into two groups: the study group who will receive standard of care with the addition of preoperative coronary computed tomographic angiography (CT group), and the control group that will receive standard of care (angiography group). The primary endpoint will be the rate of successful wire crossing in ≤ 60 min in complex CTO (J-CTO ≥ 2). Wire crossing will be considered successful if TIMI flow 3 is restored and residual stenosis is < 30%. The safety endpoint will be mortality due to the intervention or major adverse cardiac events (MACE). Secondary endpoints are success rates at any time; total time of PCI; time of wire crossing; rate of PCI complications; radiation levels during PCI; volume of iodine contrast medium administered; and cost of the PCI.

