## Assignment of interventions: blinding

### Who will be blinded {17a}

This is an open-label study for the patient and treating cardiologist, but blinded for two cardiologists who will evaluate TIMI flow and residual stenosis after CTO-PCI.

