### Adverse event reporting and harms {22}

All adverse events have to be registered in the eCRF. An adverse event is considered as serious if there is death or life-threatening circumstances, inpatient or prolonged hospitalisation, persistent or significant incapacity or substantial disruption of the ability to conduct normal life functions, congenital anomaly or an event judged as serious by the Investigator.

The medical judgement of the investigator could manage to declare some other events considered as potentially serious (especially some biological anomalies). Expected serious adverse events and unexpected serious adverse events will have to be distinguished.

The investigator must, for each serious or non-serious adverse event, describe them on a form in the eCRF. The etiological diagnostic (rather than symptom), the date of the beginning, the seriousness, the intensity, the action taken with the experimental product or the study procedure, the corrective treatment administered and the causal link between treatment or procedure and serious adverse event have to be described. When the event is considered as serious, the investigator has to inform the trial steering committee immediately after having known of the events. Within 8 days after the declaration, the investigator may provide additional relevant information to the trial steering committee. If a patient declares a serious adverse event, he will be followed until the resolution of this adverse event, a stabilisation considered as tolerable or a return to the previous statement even if the patient is withdrawn from the study. Any serious adverse event associated to a study participant has to be declared from the date of consent form signature and during all the follow-up duration. If the serious adverse event is related to the study procedure, there is no time limitation of participant follow-up.

Risks related with the CT scan, object of our evaluation: as CT scan can be performed as part of standard of care for pathology diagnosis, there is no additional risk related to this investigation performed in the study. Risks will be the same risks as those related to the angiography necessary to visualise coronary arteries before and during the recanalisation procedure, as the contrast medium used is the same:IrradiationContrast-induced nephropathy in patients with renal insufficiencyAllergic reaction to radiographic contrast media

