## Discussion

This randomised trial will provide insight into whether pre-procedural CCTA as opposed to conventional angiography for planning of CTO-PCI yield higher success rates of wire crossing in ≤60 min. Potential benefits of CCTA include shorter successful procedure times of CTO-PCI leading to less irradiation and contrast medium with lower complication rates.

This will be the second randomised controlled trial to investigate the impact of pre-procedural CCTA on CTO-PCI. Hong et al. [11] conducted a trial to test whether success rates of CTO-PCI increased when including pre-procedural CCTA as part of the treatment regimen, and found that including CCTA increased success rate (187(94%) versus 168(84%)), reduced MACEs (8(4%) vs. 10(5%)), but had higher cardiac-related deaths (1(0.5%) versus 0(0%)) and non-related cardiac deaths (2(1%) versus 0(0%)). Their study design did have some important flaws, which will be addressed in the present study. First, the previous trial enrolled any patient with CTO, whereas the present trial will only enrol patients with complex CTO (J-CTO≥2). The benefits of CCTA in addition to conventional angiography might be realised in more difficult cases of CTO. Moreover, the success of PCI in the previous study was less strict as suboptimal TIMI 2 flow was considered successful, whereas TIMI 3 flow will be considered successful in the present study. Second, the previous study, which was conducted at 12 centres, had a long inclusion period spanning 5 years and 9 months, whereas the present multi-centre study will have a 24-month inclusion period to reduce heterogeneity among patients, and with a higher inclusion rate to avoid potential selection bias. Third, the previous study relied on previous-generation CT scanning systems and protocols, whereas the present study will utilise current-generation equipment and protocols. Finally, the definition of the primary endpoint in the previous study compared success rates for any procedural time, whereas the present study will compare success rates only in cases where procedural time was <60 min.

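### The tamponade item of MACE counts only pericardiocentesis, so a surgically drained tamponade is left out; the haemoglobin item does not say how transfusion is handled (minor)

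*Protocol article*

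**What the plan says.** Outcomes {12} lists the events that make up the rate of PCI complications: death, tamponade, myocardial infarction, stroke and major bleeding. Two of the entries carry a qualifier. Tamponade is worded as "coronary perforation with cardiac tamponade requiring pericardiocentesis", and the list ends with "stroke, major bleeding with loss of haemoglobin > 3 g/dl".

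The same composite serves the safety endpoint. The abstract states: "The safety endpoint will be mortality due to the intervention or major adverse cardiac events (MACE". Statistical methods {20a} commits to comparing complications between the arms by absolute and relative risk.

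Adverse events are also collected separately. Adverse event reporting and harms {22} says "All adverse events have to be registered in the eCRF", and requires for each event, serious or not, that "the corrective treatment administered and the causal link between treatment or procedure and serious adverse event have to be described".

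On assessment, Who will be blinded {17a} says: "This is an open-label study for the patient and treating cardiologist, but blinded for two cardiologists who will evaluate TIMI flow and residual stenosis". The article describes no blinded review of MACE.

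**The concern.** A complication endpoint should count events of equal or greater severity alike. The tamponade item is tied to one way of draining the pericardium. A tamponade that needed surgery is at least as serious as one relieved by needle, yet as written it falls outside the item. Perforation is also close to the trial's rationale: the Discussion names wire perforation among the risks of longer procedures and hopes for fewer complications with CCTA.

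The bleeding item raises a weaker form of the question. It rests on a measured fall in haemoglobin, and transfusion before the later measurement restores part of that fall. The article gives neither a correction nor an alternative criterion for transfused patients.

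At stake is the completeness of a composite in which only a handful of events can be expected.

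**Working it through.** **1. Which events the list counts.** This is a matter of wording, and the plan gives no figure to reproduce. Applying Outcomes {12} literally:

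| Event | Meets its own item? | Recorded under {22}? |
|---|---|---|
| Perforation, tamponade, pericardiocentesis | Yes | Yes |
| Perforation, tamponade, surgical drainage only | No | Yes, with corrective treatment |
| Bleed, transfused, measured fall above 3 g/dl | Yes | Yes |
| Bleed, transfused, true loss above 3 g/dl but measured fall 3 g/dl or less | No | Yes, with corrective treatment |

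The second and fourth rows enter the MACE rate only if another item, such as death, is also met. No other section adds surgical drainage or transfusion to the list.

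**2. How far transfusion could mask a bleed.** The article does not give the haemoglobin rise per transfused unit. I assume about 1.0 g/dl, with a range of 0.7 to 1.3. Let L be the true loss, u the units given before the later sample and k the rise per unit:

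- measured fall = L − u × k
- the item is missed when L is above 3 but no more than 3 + u × k

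For u = 2, the upper limit of the missed range is 3 + 2 × 1.0 = 5.0 g/dl (3 + 2 × 0.7 = 4.4; 3 + 2 × 1.3 = 5.6).

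For a true loss of 4.5 g/dl and two units:

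- k = 1.0: 4.5 − 2.0 = 2.5 g/dl, not counted
- k = 1.3: 4.5 − 2.6 = 1.9 g/dl, not counted
- k = 0.7: 4.5 − 1.4 = 3.1 g/dl, counted

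The mechanism is possible but depends on assumed values. It also assumes that the loss is read from a sample taken after transfusion, which the article does not state. The concomitant care section {11d} places post-procedure sampling one day after PCI and names haematocrit. Outcomes {12} says haemoglobin is recorded after PCI without a time. Table 2 places blood sampling at 2 to 4 days. The sample that defines the loss is therefore not fixed.

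**3. Scale of the composite.** The sample size section {14} gives 65 patients per arm. The Discussion quotes MACE rates of 4% and 5% from the previous randomised trial. If they applied here:

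- per arm: 65 × 0.04 = 2.6 and 65 × 0.05 = 3.25 events
- in total: 130 × 0.04 = 5.2 and 130 × 0.05 = 6.5 events
- one event in one arm: 1/65 = 1.5 percentage points

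The article gives no frequency of surgically drained tamponade or of transfused bleeding, so the expected number of uncounted events cannot be derived.

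**The case against.** The strongest reply is that nothing is lost from the safety data. Every adverse event is recorded with its corrective treatment, so the affected cases can be found and counted under a wider definition. This stands, and it makes the change cheap. It does not put those cases into the MACE rate that the plan compares between arms.

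It can also be said that the pericardiocentesis phrase is a severity qualifier. That is a fair reading of its intent, but as a severity qualifier it should admit surgical drainage, and the wording does not. Detailed event rules may sit in a fuller document that is not shown; the list in the article is nevertheless specific on this item.

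Three stronger readings are tempting and are not supported:

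- *Both items depend on how the event was treated.* Only the tamponade item does. The bleeding item is a laboratory threshold, and transfusion affects it only indirectly.
- *Open-label management biases the comparison.* Operators know the arm and no masked MACE review is described, but nothing in the article suggests that knowing whether a CT was done would steer the choice between needle and surgery, or the decision to transfuse. What is shown is possible under-counting in either arm.
- *The wording makes the result fragile because one event shifts an arm by 1.5 points.* That shift follows from 65 patients per arm and holds under any definition. The quoted rates also come from a trial that, per the Discussion, enrolled any CTO, and its MACE definition is not shown.

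**Conclusion.** The point holds in a narrow form, as a minor one. As written, a perforation with tamponade drained surgically is left out of both the complication and the safety endpoint unless another item applies; this rests on the wording alone. That the bleeding item takes no account of transfusion is a secondary gap, which matters only when the measured fall is blunted to 3 g/dl or less. Its illustrated reach (true losses up to about 5 g/dl after two units, range 4.4 to 5.6) rests on an assumed rise per unit.

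The number of events affected is unknown and probably low, against a composite of roughly 5 to 7 events in total if the quoted rates apply. The primary endpoint is untouched.

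**What to change.** In Outcomes {12}:

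1. Extend the tamponade item so that it counts perforation with tamponade requiring drainage by either pericardiocentesis or surgery.
2. Compute the haemoglobin loss with a pre-specified correction: measured fall plus a fixed amount in g/dl for each unit transfused between the two samples. State that amount and name the two samples.

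Take drainage type and transfused units from the corrective-treatment information that {22} already requires, checking that the number of units is captured. Settle both rules before complications are compared between arms, and apply them identically to all patients.

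These are counting rules only and alter no care. An undrained tamponade would remain outside the item, which is consistent with a severity qualifier. The cost is two phrases in the endpoint definition, an amendment since the trial has started, and a possibly slightly higher reported MACE rate. No additional patients, procedures or blinded reclassification are needed.

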### Intervention description {11a}

#### Preoperative assessment

The following assessments will be performed as part of the standard of care for the diagnosis of CTO:Conventional coronary angiographyIf symptoms and viability are not established through angiography, the patient will undergo one of the following:aStress electrocardiogram (ECG)bCardiac magnetic resonance imaging (MRI)cStress echocardiographydMyocardial scintigraphyCollection of biological markers: troponin, creatine kinase, creatinine, clearance of creatinine, haemoglobin. Preoperative angiography will be performed for all patients in ambulatory settings under local anaesthesia, with either a radial artery or femoral artery approach, with the former being the first choice if the artery is of good quality. An introducer sheath measuring 4 or 5 French (Fr.) is advanced within the artery using the Seldinger technique, and a catheter is advanced through the introducer up to the heart. A 6–8 cc iodine contrast injection in the coronary artery ostia allows visualisation of coronary artery anatomy under radiography. A picture registration is obtained and archived for planning of CTO-PCI. During the procedure heparin and nitrates are administrated.

If conventional angiography indicates a J-CTO score ≥2, the patient will be enrolled in the study, if they meet the eligibility criteria. Patients will then be randomly allocated to the CT group or angiography group. Patients in the CT group will undergo an additional CCTA scan (GE CT Revolution Scan 256; Iomeron 350 iodine contrast). The total dose length product (DLP, mGy/cm^2^) and computed tomography dose index (CTDI, mGy) will be recorded. Iodine contrast for the CCTA will be 55ml (10ml saline–55ml Iomeron 350–20ml saline at 5ml/s).

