The primary endpoint, that is the success rate of difficult CTO-PCI in ≤60 min wire manipulation, will be assessed for each of the three datasets, i.e. intention-to-treat, per-protocol and as-treated, after the CTO-PCI (D0, Table 2). The TIMI flow and residual stenosis after the procedure will be recorded for each of the three datasets, i.e. intention-to-treat, per-protocol and as-treated, and will be assessed at immediate follow-up (D0 + 2 to 4 days) and final follow-up (D0 + 180 days). Laboratory parameters will be recorded for each of the three datasets, i.e. intention-to-treat, per-protocol and as-treated, and will be assessed at immediate follow-up (D0 + 2 to 4 days). The success rate of the complex CTO-PCI between both groups will be calculated for each of the three datasets, i.e. intention-to-treat, per-protocol and as-treated, at immediate follow-up CTO-PCI (D0 + 2 to 4 days) and final follow-up (D0 + 180 days). For all three datasets, i.e. Intention-to-treat, Per-protocol and As-treated, all adverse events will be recorded according to the corresponding system organ class (SOC) and preferred term (PT) using the MedDRA terminology. Creatinine levels after the CTO-PCI, summarising the renal adverse events, will be described in both groups. Symptoms (angina CCS class/dyspnea NYHA class), MACE, and renal failure will be evaluated at the CTO-PCI visit and end of study visit.

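### Radiation and contrast are compared during PCI only, so these endpoints cannot show whether the CCTA strategy lowers the patient's total exposure

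*Protocol article*

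**What the plan says.** Outcomes {12} in the protocol article lists two exposure endpoints among the secondary objectives, both limited to the PCI:

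- Contrast: "Volume of iodine contrast medium administered during PCI (millilitres").
- Radiation: "Radiation levels during PCI expressed as transferred kinetic energy (air Kerma, Gy), dose area product (DAP, mGycm^2^), and fluoroscopy time (minutes").

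The section Preoperative assessment, under Intervention description {11a}, sets out the difference between the groups after allocation: "Patients in the CT group will undergo an additional CCTA scan". It gives the volume, "Iodine contrast for the CCTA will be 55ml", and says that the dose length product and the "computed tomography dose index (CTDI, mGy) will be recorded". No stated between-group comparison uses these CT quantities.

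The scope varies across the article. Objectives {7} and the endpoint list closing Background and rationale {6a} name radiation and injected contrast with no restriction to the PCI. The Abstract restricts radiation to the PCI but not contrast. The cost item in Outcomes {12} does name the CT scan for the CT group.

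The Discussion describes the potential benefit of CCTA as shorter successful procedures "leading to less irradiation and contrast medium with lower complication rates". Background and rationale {6a} also lists less radiation and less contrast among the things CCTA could improve.

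**The concern.** The trial compares two strategies: standard care, and standard care plus a CCTA. For a patient or a clinic choosing between them, the relevant exposure is everything received from randomisation onward. The endpoints count only the PCI part.

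The uncounted part falls on one side. Diagnostic angiography precedes randomisation and is done in both groups, so leaving it out creates no imbalance. The CCTA follows randomisation and is given in the CT group only.

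At stake is what the trial may say about exposure. A lower PCI volume in the CT group could be reported as a contrast saving from CCTA although CT-group patients received the same or more contrast overall. The same reversal is possible for radiation.

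**Working it through.** The article states no power, expected mean or SD for radiation or contrast, so there is no figure of its own to reproduce. The check is the arithmetic of the two definitions, followed by an illustration at the planned size.

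**Inputs**

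- CCTA contrast: 55 ml per scanned patient in the CT group, 0 ml in the control group (Preoperative assessment).
- Group size: 65 per group (Sample size {14}).
- Test: two-tailed t-test for normally distributed data, p < 0.05 (Statistical methods {20a}).
- SD of PCI contrast volume: not in the article; assumed 60 to 150 ml.

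**Step 1: relation between the two definitions.** Let d be the mean PCI contrast in the CT group minus that in the control group. If every CT-group patient is scanned and no control patient is:

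total difference = d + 55 ml

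Total contrast is therefore lower in the CT group only if d < −55 ml. For a PCI saving of 30 ml, d = −30 and the total difference is −30 + 55 = +25 ml: less contrast on the PCI-only endpoint, more in total.

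**Step 2: how often would the PCI-only test favour CCTA?** By the normal approximation for two means:

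probability = Φ( s / (SD × √(2/65)) − 1.96 ), where s is the true PCI saving.

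Worked case, s = 55 and SD = 100: the standard error is 100 × √(2/65) = 17.54; 55 / 17.54 = 3.136; 3.136 − 1.96 = 1.176; Φ(1.176) = 0.88.

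| Assumed SD (ml) | PCI saving 55 ml (totals equal) | PCI saving 30 ml (CT group +25 ml in total) |
|---|---|---|
| 60 | 0.999 | 0.81 |
| 80 | 0.975 | 0.57 |
| 100 | 0.88 | 0.40 |
| 120 | 0.74 | 0.30 |
| 150 | 0.55 | 0.21 |

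In each row the PCI-only test is right about the PCI. The table shows how often a significant result would appear that total exposure does not share. Adding a constant 55 ml to every scanned patient leaves the SD unchanged, so when totals are equal a test on totals would favour CCTA with probability 0.05 / 2 = 0.025.

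**Step 3: radiation.** The same identity holds: total difference = PCI difference + CCTA dose. The article gives neither an expected PCI dose nor an expected dose length product, so the offset cannot be computed. The recorded quantities also cannot be added directly, because air kerma, dose area product, fluoroscopy time and dose length product are on different scales.

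**The case against.** The strongest reply is that the endpoints are labelled as PCI measures and do what the label says. A randomised comparison of PCI exposure is unbiased for PCI exposure, and the Discussion words the benefit as potential and ties it to shorter procedures. The CCTA exposure is disclosed and recoverable: the volume is fixed, and the CT dose quantities are recorded. The article also remarks, under Adverse event reporting and harms {22}, that 55 ml is low compared with the volume used in angiography and PCI.

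Much of this stands. A reader might infer that the comparison is biased by construction. It is not: it answers a narrower question, and the error would arise only on reading it as the exposure of the strategy. The reply does not settle the matter, however, because Objectives {7} and Background and rationale {6a} state the aim without the PCI limit and so invite that reading. Nor does the remark that 55 ml is low help, since the relevant yardstick is the between-group difference, not the volume of a whole procedure.

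A second tempting inference is that renal safety lacks a comparable baseline, since one sentence in Plans for assessment and collection of outcomes {18a} reads "Creatinine levels after the CTO-PCI, summarising the renal adverse events, will be described in both groups". The documents do not support this. Table 2 schedules blood sampling at enrolment in both groups, before the CT scan. The blood sample before PCI is nowhere called a baseline. Renal adverse events are to be assessed after CCTA as well, and post-PCI creatinine in the CT group is measured after both contrast exposures.

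A third is to set the 55 ml against the contrast dose above 100 ml that the article links to renal complications. The article does not say whether that figure is per procedure or cumulative, and Table 2 places the scan 1 to 30 days before the PCI, so the comparison is left out here.

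**Conclusion.** The point holds as a mismatch between the stated aim and the endpoint definitions. The PCI-only measures support conclusions about the procedure; they do not support a conclusion that the CCTA strategy lowers patient exposure.

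For contrast the size is exact: 55 ml per scanned patient, so the break-even PCI saving is 55 ml, assuming every CT-group patient and no control patient is scanned. The probabilities (0.55 to 0.999 with equal totals, 0.21 to 0.81 with 25 ml more in the CT group) rest on assumed SDs and a normal approximation; they illustrate the risk and do not predict the result. For radiation only the direction of the omission is known. A reader might conclude that CT-group patients will receive more of both; the documents show that this is possible and give nothing to show that it is likely.

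Two secondary endpoints are affected. The primary endpoint, the sample size and the randomisation are not. The dose length product unit, printed as mGy/cm², is a notation slip to be corrected and not an obstacle to conversion.

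**What to change.** 1. Keep the PCI-only contrast and radiation endpoints, labelled as procedural exposure.
2. Add total contrast from randomisation: PCI volume plus CCTA volume.
3. Add total radiation from randomisation on a common scale, for example effective dose from the PCI dose area product and the CCTA dose length product, with conversion factors stated in advance. Correct the dose length product unit to mGy·cm.
4. State that any conclusion about exposure under the CCTA strategy rests on the totals, and bring the Abstract, Background and Objectives {7} into line with Outcomes {12}.

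The contrast total needs no new data, because the CCTA volume is specified, and the CT dose quantities are already recorded. The costs are a little more analysis, a dose conversion that is only approximate, and a result that may look less favourable to CCTA. The definitions should be fixed before any comparative results are seen.
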